
#### Testing protocol

2.13.3

According to new model of Qigong scientific research^[75]^ “Two-way layout, correlated detection and mutual paraphrase (2-way layout refers to design both schemes of Qigong internal operation and external detection; the whole design project includes a subjective part and an objective part. Correlated detection refers to detect objective indexes from outside and subjective operational indexes from inside simultaneously during examination. Mutual paraphrase refers to give the meaning of the experimental result by explaining internal and external indexes to each other.)” designed by [name] of BUCM. At baseline, 6 weeks (at the mid-point of intervention), 11 weeks (at the end of intervention), we designed testing scheme for *TCPSQ* internal operation (such as successively practicing feet grasping the ground (I) → stretch the waist and sink the crotch (II) → lowering the shoulders and elbows (III) → head upright and neck relaxation (IV) → the tongue tip close to the hard palate (V) → abdominal breathing (VI) → whole body relaxation (VII), and so on) and external detection (synchronous detection of bioelectrical activity of cortical neurons, static biomechanical balance of spinal column, degree of thoracic breathing and abdominal breathing, and electrical activity of the heart in *TCPSQ* state). And participants will fill in the self-made internal operation of *TCPSQ* state self-evaluation scale when the external detection is finished. At the same time, we will also performing synchronous detection of bioelectrical activity of cortical neurons, static biomechanical balance of spinal column, degree of thoracic breathing and abdominal breathing, and electrical activity of the heart in natural stance state, detection of special static biomechanical balance of spinal column (such as single foot and closed eye, single foot and open eyes), dynamic biomechanical balance of spinal column, morphological balance of spinal column, cardiopulmonary function, and the physical and psychological self-reported scales measurement. In addition, *TCPSQ* internal operations are carried out under the prerecorded instructions and it should be noted that all participants at baseline and participants in the control group just imitating internal operations under the prerecorded instructions.

#### Secondary outcomes

2.13.4

Cardiopulmonary function, personality, self-esteem, quality of sleep, constitution in Chinese medicine, symptoms induced by spinal problems, and self-evaluation of Qigong training were regarded as secondary outcomes.

1.Cardiopulmonary function will be evaluated indirectly by blood pressure (BP), heart rate (HR). Also BP and HR will be tested by *HEM-746C electric sphygmomanometers* produced by the Omron Corp., China.2.Personality will be measured using EPQ-RSC revised by Gong Yaoxian and Chen Zhonggeng, etc. It consists of a 48-item self-report scale with 4 subscales: an extraversion/introversion scale (lower scores indicate more introversion), a neuroticism/stability scale (higher scores indicate greater emotional instability), a psychoticism/socialization scale (higher scores indicate being more reclusive, indifferent to others, and intransigent), and a lie scale. Only the first 3 personality traits were included in our analysis. The lie scale was used to assess the acceptability of respondents’ answers. Participants provided a yes or no response, and responses are scored 1or 0, respectively, except for some reverse-scored items. These 4 traits have been shown to have good factorial similarity across 34 countries in a study that analyzed gender-specific data. In the current sample, Cronbach's coefficient for the EPQ-RSC ranged from 0.62 to 0.72.^[93,94]^3.RSES will be adopted to measure self-esteem. We will use the Chinese version of RSES translated by Ji and Yu.^[95]^ It consists of 10 items, and the total score ranges from 10 to 40. Higher scores indicate higher self-esteem.4.Quality of sleep will be indexed by PSQI.^[96]^ The locally validated Chinese version of the PSQI is a self-report questionnaire that assesses multiple dimensions of sleep over the past month. Nineteen individual items generate 7 component scores: subjective sleep quality, sleep latency, sleep duration, habitual sleep efficiency, sleep disturbances, use of sleeping medication, and daytime dysfunction. The sum of the 7 component scores ranges from 0 to 21; The sum of the 7 component scores yields one global score of subjective sleep quality, higher scores represent poorer subjective sleep quality.5.Traditional Chinese Medicine body constitution will be evaluated with CCMQ. CCMQ is a self-rating scale with good reliability and validity that consists of 60 items scored on a 5-point scale, ranging from 1 (not at all) to 5 (very much). It has 9 subscales which assess one type of TCM constitution individually, including neutral constitution, Qi-deficiency constitution, Yang-deficiency constitution, Yin-deficiency constitution, Phlegm-damp constitution, Damp-heat constitution, Blood-stagnation constitution, Qi-stagnation constitution, and Special diathesis constitution. For each item, subjects selected 1 from 5 answers (not at all, few, sometimes, often, always), and given a respective score (1–5). For each subscale, the original score was first calculated by summing of the scores for each item. The derived score of each subscale was calculated from the following formula: (original score−the possible lowest score of the subscale)/(possible highest score-possible lowest score) × 100, ranging from 0 to 100 points. Neutral constitution referred to the patients with derived scores of the 8 unbalanced constitutions being <40 points, and the derived score of the Neutral constitution being ≥60 points. If the score of any constitution subscale was ≥40 points, unbalanced constitutions were diagnosed. Patients with 2 or more constitutional types ≥40 points, subjects were diagnosed with constitution of the highest subscale score.^[97,98]^6.SQSSP will be used to evaluate subjective feelings of symptoms induced by spinal problems. It consists of 10 items that indicate 9 basic symptom factors induced by spinal problems: the relaxation or tensity or pain and fatigue of various parts of body, the degree of limitation in various parts of body, sense of suppression in the chest, palpitation, fatigue, emotional stability, insomnia, quality of life, and self-feeling in present.7.SQTSS will be adopted to make self-evaluation about Qigong training. It has 2 subscales which assess self-evaluation during training and self-evaluation after training. The Self-made Qigong Training Self-evaluation Scale, from the perspective of participants themselves, provides a lot of information about training quality and effects of Qigong training on physiology, respiratory function, and psychology.

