### Statistical analysis

2.16

Collected data will be recorded on standardized forms. Descriptive statistics will be calculated for dependent and independent variables. This analysis will include summary statistics of demographic information and outcome measures. Continuous variables will be summarized as mean (SD) ± standard deviation for normal distribution, and median (IQR) ± interquartile range for non-normal distribution. Normality will be tested using *Kolmogorov–Smirnov* test and categorical variables will be presented with frequencies or percentages. Appropriate transformations will be applied in cases of non-normal distribution. For the variables with a normal distribution, differences in terms of outcomes between groups will be compared using an independent *T-*test. If the variables have a non-normal distribution of ordinal level, statistical comparison between groups will be made by using the *Mann– Whitney U* test even after suitable transformations. Measures with a discrete distribution will be expressed as percentages and analyzed by the *X*^*2*^ or Fisher's exact test as appropriate. Subgroup analysis will be performed according to participants’ gender, personality, and constitution of TCM. Analysis of variance (ANOVA) will be used for the repeated measurement data, and *post-hoc* comparison between groups at different assessment time points will be conducted using multiple comparisons with adjustment to the type 1 error rate. Analysis of the primary and secondary outcomes will be on the basis of intention-to-treat (ITT) population and per-protocol (PP) population. The result of the ITT analysis will be compared with that of the PP analysis to check whether the results are consistent or not. If the statistical results of the ITT and PP population data are the same, the results will be deemed to be reliable; if they are contrary, we intend to adopt the results of the ITT population. The method of processing missing data will be the last observation carried forward (LOCF). This refers to assigning the last observed value of the end point indicator to the subsequent missing evaluation point; that is, the last observation response will be considered to be the study end point. Safety will be evaluated by tabulations of AEs, and will be presented with descriptive statistics for each group. A chi-square test or a Fisher's exact test will be used to compare the frequency difference in AEs between the 2 groups, and severe AEs will be listed in detail. To explore potential factors which might influence adherence, a logistic regression model and a linear mixed-effects model will be used and adjusted for potential confounders. Adherence-related data will be taken from training log records. All statistical tests will be implemented using IBM SPSS 21.0 with bilateral inspection. The level of statistical significance is assumed at 2-sided *P* value <.05.

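### The CCMQ constitution rules conflict as written: everyone who meets the neutral definition is also unbalanced, and the highest-score rule can return a neutral type that the definition excludes

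*Protocol article*

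**What the plan says.** All the scoring rules stand in section 2.13.4 (Secondary outcomes), item 5.

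- Subscales: "It has 9 subscales which assess one type of TCM constitution individually, including neutral constitution". The other eight are the unbalanced types. Each derived score runs from 0 to 100.
- Neutral, first condition: "Neutral constitution referred to the patients with derived scores of the 8 unbalanced constitutions being <40 points".
- Neutral, second condition: "the derived score of the Neutral constitution being ≥60 points".
- Unbalanced: "If the score of any constitution subscale was ≥40 points, unbalanced constitutions were diagnosed".
- More than one type at or above the cut-off: "Patients with 2 or more constitutional types ≥40 points, subjects were diagnosed with constitution of the highest subscale score".

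The classification is used again in section 2.16 (Statistical analysis): "Subgroup analysis will be performed according to participants", where the factors named are gender, personality and TCM constitution. The Discussion (section 5) also promises to explore how the training works in students with different constitutions. Constitution is itself listed as a secondary outcome.

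**The concern.** The neutral definition confines the 40-point cut-off to the eight unbalanced subscales. The two rules that follow drop that limit and speak of any constitution subscale, or of constitutional types in general, shortly after neutral was listed as one of the nine. A programmer who takes these sentences at face value would apply the cut-off, and take the maximum, over nine scores. Two contradictions follow. The neutral and unbalanced classes overlap, and the highest-score rule can hand out a neutral label that the neutral definition refuses.

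At stake is the constitution class. It decides membership in one of the three planned subgroup analyses. It also decides the secondary outcome if that outcome is reported as a type and not as subscale scores. If the conflict is found only once the data are in hand, someone must choose a reading at that point, which is avoidable analytic freedom in a trial of 80 participants.

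**Working it through.** The article prints no figure to reproduce here, so the check is one of logic. Let N be the neutral derived score and U the highest of the eight unbalanced derived scores. The rules as printed in section 2.13.4, item 5, are:

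- Rule 1 (neutral): U < 40 and N ≥ 60.
- Rule 2 (unbalanced): N ≥ 40 or U ≥ 40, since any of the nine subscales counts.
- Rule 3 (type): if two or more of the nine are ≥ 40, take the type with the highest score.

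**Rule 1 against rule 2.** N ≥ 60 implies N ≥ 40, so rule 1 always implies rule 2. Example: N = 75 and all others 20 is neutral by rule 1 and unbalanced by rule 2.

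**Rule 1 against rule 3.** Take N = 70, Qi-deficiency = 45 and the rest low. Two types are ≥ 40 and the highest is neutral, so rule 3 returns neutral. Rule 1 excludes this person because U = 45 is not below 40. With N = 55 and one unbalanced score of 45, rule 3 again returns neutral, although both conditions of rule 1 fail.

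**Enumeration.** The rules were applied to every integer pair N = 0–100, U = 0–100 (101 × 101 = 10,201 pairs), with the other seven unbalanced scores set to 0:

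| Situation | Pairs | Arithmetic |
|---|---|---|
| Meets rule 1 | 1,640 | 41 values of N × 40 values of U |
| Of these, also meets rule 2 | 1,640 | all |
| Rule 3 returns neutral (N > U ≥ 40) | 1,830 | 61 × 60 / 2 |
| Of these, fails rule 1 | 1,830 | all, because U ≥ 40 |
| Unbalanced by rule 2, but no unbalanced type ≥ 40 and not neutral (N 40–59, U < 40) | 800 | 20 × 40 |
| No class at all (N < 40, U < 40) | 1,600 | 40 × 40 |

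**After limiting rules 2 and 3 to the eight unbalanced subscales.** Unbalanced then means U ≥ 40, which cannot coexist with rule 1, and the highest score is taken among the eight only. Both contradictions disappear. The pairs with U < 40 and N < 60 now have no class: 60 × 40 = 2,400, which is the last two rows together (800 + 1,600).

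The pair counts show how the rules behave. They are not expected participant frequencies, because real scores are not spread evenly over the grid.

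**The case against.** The strongest reply is that the intended meaning can be seen from context. The 40-point cut-off is introduced for the eight unbalanced subscales, neutral has its own threshold of 60, and the unbalanced sentence reads naturally as the complement of the condition just before it. The paragraph also summarises a published questionnaire, with references, so the scoring actually used may follow the instrument and not these sentences. Much of this stands. The eight-subscale reading is probably what is meant, and it removes both contradictions. But the article does not say so. It states numerical rules in complete sentences, and followed as printed they conflict.

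Three stronger readings are tempting, and the documents do not support them.

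- A reader might infer that a particular share of participants will be misclassified. Any such percentage needs means, standard deviations and correlations of the nine scores. The documents give none, and a simulation would mostly return its own assumptions.
- A reader might infer that the between-arm comparison on constitution is wrong. Section 2.13.4 also yields continuous derived scores, and section 2.16 provides methods for continuous as well as discrete measures. If the scores are compared, the conflict does not touch that comparison.
- A reader might infer that the unclassified group results from the contradiction. It does not: those participants fall outside both classes under the intended reading too. That is a separate and lesser gap, which the instrument's own scoring may settle.

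**Conclusion.** The point holds as a defect of wording in a stated scoring rule. As printed, all participants who satisfy the neutral definition are also diagnosed unbalanced. Whenever neutral is the highest of two or more scores at or above 40, the highest-score rule returns a class that the definition excludes. Neither statement needs an assumption about the data.

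The consequence is conditional on the rules being coded literally. In that case membership in the constitution subgroups is misassigned, and so is the secondary outcome if it is analysed as a category. How many of the 80 participants would be affected cannot be estimated from the documents. The weight is modest, between a minor clarification and a change that should be made, because only one secondary outcome and one subgroup factor are involved.

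**What to change.** Reword the two sentences in section 2.13.4, item 5, so that both refer to the eight unbalanced subscales only:

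- a participant is unbalanced if at least one of the eight is ≥ 40;
- the type is the one with the highest score among those eight.

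The neutral definition stays as it is. As a secondary matter, state how participants with all eight scores below 40 and neutral below 60 are handled under the instrument's scoring, and keep them in the denominator.

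The cost is a few words in the protocol or analysis plan and a matching line in the scoring syntax, settled before the data are analysed. No new data and no change to the sample size are needed.

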
### Adverse events collection procedure and safety measurements

2.14

As far as we know, AEs will be defined as any undesirable experience participants endure during the trial period, regardless of whether or not it is associated with the intervention, there are no adverse events reported about *TCPSQ*. If any unexpected AEs occur, all unexpected AEs related to *TCPSQ* will be reported to the researchers or the project manager and the causality with *TCPSQ* intervention will be analyzed regardless of the investigators’ assessments of causality and the coaches or project managers will provide the corresponding treatment to the participant. All details of AEs (defined as any functional lesion caused by the intervention, such as headache, dizziness or vertigo, distension of head, tinnitus, stuffiness in the chest and worsening shortness of breath, heart-pounding or palpitations, muscular soreness or pain, profuse cold perspiration, irritability, neurasthenia, hallucination and paranoia, psychological stress and so on), such as whether expected or not, relatedness to the study, time of occurrence, severity, management, and causality to the intervention will be recorded on Case Report Forms (CRFs) during the intervention period. All AEs will be followed-up from the date they are brought to the investigator's attention until resolution.

Serious AEs are defined that is life-threatening, requires hospitalization, results in persistent or significant disability/incapacity or death. If serious AEs happen, the researchers will report to the primary investigator and ethics committee within 24 hours, who will make a decision on whether the participant needs to withdraw from the study. The causality between serious adverse events and intervention will also be analyzed.

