**Method/design::**

We will conduct a randomized, assessor, and statistician blinded, parallel-controlled trial comparing the beneficial effect of TCPSQ in college students. A total of 80 eligible college students from the Beijing University of Chinese Medicine (BUCM) will be recruited and randomly allocated into TCPSQ training or unaltered lifestyle control group according 1:1 allocation ratio with allocation concealment. TCPSQ intervention will last 10 weeks. The study period is 18 weeks including a 10-week supervised intervention and a 8-week follow-up. The relevant physical and psychological outcomes, adverse events, and safety will be evaluated at baseline, 6 weeks (at the mid-point of intervention), 11 weeks (at the end of intervention), and 19 weeks (after the 8-week follow-up period) by blinded independent outcome assessors.

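### The protocol gives two conflicting adverse event definitions and two conflicting collection windows, and does not say which supplies the planned between-group test

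*Protocol article*

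**What the plan says.** Section 2.14 opens with a broad definition: "AEs will be defined as any undesirable experience participants endure during the trial period, regardless of whether or not it is associated with the intervention". The next sentence narrows what is passed on: "all unexpected AEs related to *TCPSQ* will be reported to the researchers or the project manager". The sentence on the CRF then carries a different definition: "All details of AEs (defined as any functional lesion caused by the intervention". It goes on to a list of example symptoms such as headache, dizziness, muscle soreness and irritability. For each event the CRF is to hold, among other items, "relatedness to the study, time of occurrence, severity, management, and causality to the intervention", and these details "will be recorded on Case Report Forms (CRFs) during the intervention period".

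The abstract (Method/design) gives a longer window. It says "The relevant physical and psychological outcomes, adverse events, and safety will be evaluated at baseline, 6 weeks", then at week 11, "and 19 weeks (after the 8-week follow-up period) by blinded independent outcome assessors".

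Section 2.16 plans AE tabulations for each group, with a chi-square or Fisher's exact test "used to compare the frequency difference in AEs between the 2 groups". It does not say which definition or which window feeds that test.

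Three other places bear on the point. Section 2.4 gives every participant a log book that includes AE reporting. Section 2.11.2 gives the control group no training. Section 2.13.3 has controls imitate the TCPSQ operations, following recorded instructions, at the test visits.

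**The concern.** The two definitions disagree on causality. A control participant's headache is an AE under the first definition and normally not under the second. The windows disagree too: the trial period is 18 weeks (section 2.2), and the intervention period is 10 of them.

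This matters because the CRF is the only record that section 2.14 names for AE details, and the CRF sentence carries the causal definition and the shorter window. Staff who follow that sentence as written would leave out most or all control-arm events and could leave out follow-up events. The between-group test would then set attributed events in one arm against almost none in the other. Many of the listed symptoms are likely in students whatever their arm, so the filter would not be harmless. The error can also run the other way: where attribution is withheld, a genuine excess in the TCPSQ arm goes unrecorded.

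Safety is part of the primary aim in section 2.1. An event that was never written down cannot be recovered at the analysis, whatever the analysis plan says.

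**Working it through.** **The wording side by side**

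| Source | Cause required? | Window |
|---|---|---|
| 2.14, opening definition | No | Trial period (18 weeks) |
| 2.14, CRF sentence | Yes | Intervention period (10 weeks) |
| Abstract, Method/design | Not stated | Baseline to week 19 |
| 2.4, log book | Not stated | Not stated |
| 2.16, test | Not stated | Not stated |

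Window: 10/18 = 56% of the study weeks fall inside the CRF sentence and 8/18 = 44% fall outside it.

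**Inputs.** There are 40 participants per arm (section 2.3) and the test is two-sided at 0.05 (section 2.16). The documents give no AE rate and no figure for the AE comparison, so there is no stated result to reproduce. The true rate below is an assumption, shown over a range.

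**Step 1: how many events make the test significant if the control count is zero.** For k/40 against 0/40, the two-sided Fisher P value is 2 × C(40,k)/C(80,k).

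- k = 4: P = 0.116
- k = 5: 2 × 658,008/24,040,016 = 0.055
- k = 6: 2 × 3,838,380/300,500,200 = 0.026
- k = 8: P = 0.0053

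Six attributed events are enough.

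**Step 2: how often that happens when the true rates are equal.** Suppose each participant has an AE with the same probability p in both arms. Take the extreme case, in which no control event is counted and every TCPSQ-arm event is attributed. The chance of a significant result is P(X ≥ 6) with X ~ Binomial(40, p). The comparison column applies the all-cause definition to both arms and sums the probabilities of all tables with Fisher P < 0.05.

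| Assumed true rate | CRF definition, extreme case | All-cause definition, both arms |
|---|---|---|
| 5% | 1.4% | 0.4% |
| 10% | 21% | 1.7% |
| 20% | 84% | 2.8% |
| 30% | 99% | 2.8% |

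**Step 3: partial attribution.** At a true rate of 20%, 8 events are expected in each arm (0.20 × 40). If 8, 6 or 4 of the TCPSQ-arm events are attributed and no control event is counted, P is 0.0053, 0.026 or 0.116. The true difference is zero in all three cases.

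**The case against.** A reader might infer that AEs are recorded only in the intervention period, that the control arm cannot have any, and that the test therefore measures attribution by unblinded staff. The document does not support that reading.

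- **Window.** The CRF sentence does not exclude later recording. The abstract schedules AE evaluation at week 19, the opening definition covers the whole trial, and the log book goes to everyone. Section 2.12 also provides weekly gatherings during follow-up. What can be shown is an inconsistency, not that 44% of the study has no AE recording.
- **Control arm.** A zero count follows only if the causal definition feeds the test, and no section says so. The opening definition is the more formal one. Listing relatedness and causality as CRF items makes little sense if every entry is already caused by TCPSQ, and tabulating AEs by group presupposes control events. Controls also imitate the TCPSQ operations at test visits, so even the causal definition does not make a control event impossible.
- **Attribution.** The abstract assigns AE evaluation to blinded assessors. Section 2.14 has causality analysed whatever the investigators judged. The coaches are unblinded (section 2.10), but nothing gives attribution to them alone.
- **Size.** The rate is assumed. Section 2.14 says no AEs have been reported with TCPSQ, and at a 5% rate even the extreme case gives a false positive only about 1% of the time.
- **Status.** This is a pilot, and no stopping or efficacy decision hangs on the AE test.

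All of this stands as a limit on the claim. It does not remove the conflict: the causal wording sits in the very sentence that tells staff what to put on the form.

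**Conclusion.** The concern holds as a contradiction with a conditional consequence. Section 2.14 states two definitions that cannot both apply to an unrelated event. Its CRF window also conflicts with its own opening definition and with the abstract.

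If the CRF definition and window supply the section 2.16 test, control-arm events are close to zero by construction and events in 8 of the 18 weeks may be missed. The result would then not be a comparison of risk. In the extreme case, the chance of a falsely significant difference runs from about 1% at a true rate of 5% to 84% at 20%, against 0.4% to 2.8% with one all-cause definition. These figures rest on an assumed equal rate, 40 evaluated per arm, no control event counted and full attribution in the TCPSQ arm. Partial attribution weakens the effect.

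If the opening definition governs in practice, the test is sound, but the text does not secure that. The point is worth settling before data collection because safety is in the primary aim and unrecorded events are unlikely to be recovered.

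**What to change.** Reconcile the abstract and sections 2.4, 2.14 and 2.16:

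1. Delete the causal definition from the CRF sentence and keep the all-cause definition as the only one. The symptom list can stay as examples.
2. Record AEs on the CRF in both arms, with the same prompt, from randomisation to week 19.
3. Keep relatedness as the separate CRF field that section 2.14 already lists, and make clear that the sentence on reporting TCPSQ-related events does not limit what is recorded.
4. State in section 2.16 that the between-group comparison uses all-cause AEs over that window, and list TCPSQ-related events descriptively.

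The cost is a change of wording in the protocol and the CRF, plus slightly more CRF recording during follow-up. The log books (section 2.4) and daily activity diaries (section 2.11.3) already go to all participants, so no new contact is needed.
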